## Methods

### Objectives and hypotheses

In 2011, the Co-Venture Trial was funded by the Canadian Institutes of Health Research (CIHR) to test the 4-year impact of the Preventure programme on delaying early onset drinking and binge drinking in students as well as long-term addiction outcomes. A subsequent CIHR grant was awarded for the Neuroventure study, allowing us to add longitudinal neuroimaging measures to test the following objectives/hypotheses:Compare high-risk (IMP and SS) and low-risk youth on measures of brain structure and function to quantify neurocognitive endophenotypes of these two risk profiles prior to exposure to alcohol in adolescence. We expect to observe impaired fronto-striatal connectivity and function during response inhibition in IMP as well as altered function of frontal and sub-cortical regions (i.e., basal ganglia and ventral striatum) during reward anticipation in SS.Measure the correlates of adolescent drinking and binge drinking on the development of brain structure and function in adolescence, controlling for baseline differences in personality, cognitive profiles, and neural measures that are implicated in the predisposition to early onset alcohol misuse. By comparing youth who take up drinking to those who do not (regardless of intervention status), we will test the extent to which binge drinking trajectories are associated with delayed or altered development of fronto-striatal and fronto-limbic networks that mediate response inhibition and anticipation of reward/punishment. Three hypotheses will be examined. i) Global effects: abnormalities will be observed systematically across all measures of brain function and structure, ii) Developmental specificity: alcohol-induced abnormalities will be specific to regions and cognitive processes that are maturing in adolescence, and iii) Interaction effect: alcohol will exacerbate the abnormalities shown to characterize each high-risk group at baseline.Test causal hypotheses by testing whether delaying drinking (through the Preventure Programme) can produce observable protective effects on structural and functional brain development. By comparing high-risk youth who received intervention to those who did not, we will estimate an intervention effect on structural and functional brain outcomes, which again might be expressed globally across the brain, or more specifically in those areas developing during adolescence or most abnormal in high-risk groups (as revealed in objective 1).

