
### The Co-Venture Trial (from which the participants are recruited)

This study uses a cluster-randomized controlled design in which 31 schools (cluster) agreed to conduct annual surveys for 5 years with all consenting adolescents (*N* = 3826) who were enrolled in Grade 7 in September 2012. Schools were randomly assigned to i) be trained and assisted in the delivery of the Preventure programme to Grade 7 high-risk adolescents or ii) not be exposed to the intervention. Adolescents were screened using the SURPS [36] during their Grade 7 year and invited to participate in personality-specific Preventure workshops if they scored one standard deviation above the school mean on one of the four SURPS dimensions. The Co-Venture clinical Trial is registered on www.ClinicalTrials.gov, “Co-Venture: a Cluster Randomized Trial Investigating the Effects of Selective Intervention on Adolescent Cognitive Development and Addiction”, study NCT01655615.

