### Neuroventure: neuroimaging add-on study

#### Participants

Neuroventure will focus on high-risk students with SS and IMP personality profiles as they contribute most to the prediction of early onset substance-related behaviors in adolescence [42]. Thus, a subsample from the Co-Venture Trial of 60 high SS (30 of whom will receive the intervention), 60 high IMP (30 of whom will receive the intervention) and 30 low-risk (low SS and low IMP will not be invited to participate in the interventions) Grade 7 students (50% girls) will be invited to participate in this neuroimaging study (Please refer to Fig. 1 for the consort diagram and to Fig. 2 for the actual recruitment data). An independent informed consent from parents and adolescents will be obtained for the present study. Exclusion criteria will include major neuro-developmental disorders (e.g., autism), uncorrectable visual impairment or hearing deficits, severe mental health problems (e.g., schizophrenia, bipolar disorder), uninterruptable central nervous system medication, and any magnetic resonance imaging (MRI) contraindications (e.g., pregnancy, braces, etc.).

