#### Sample size justification

An estimated 125 subjects in total will be required to identify a moderate effect of personality group (high SS, high IMP, low-risk) on brain measures, prior to the initiation of alcohol use, with 4 covariates, critical F(2, 118) = 3.07, *p* = 0.05, 85% power. Another 25 participants will be added to the sample to allow for attrition (15% over 4 years, based on previous studies). This sample size will provide 90% power to assess moderate group differences in developmental trajectories of alcohol use (group by time interactions) within a longitudinal design with 3 repeated assessments and corrections for multiple testing, critical F(4240) = 3.40, *p* = 0.001. The current study will be sufficiently powered to detect two-year changes on functional and structural data, considering numerous previous studies of similar size showing moderate (*r* = .30) age-related activation in cortical and subcortical regions of the brain when performing fMRI tasks tapping attention and higher cognitive abilities [10]. Similar power is required to test the effects of intervention.

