#### Statistical analyses

The main objectives of the statistical analyses will be to characterize differences for fMRI, cortical thickness, VBM, DWI and behavioral measures between high (SS and IMP) and low-risk youth, binge drinkers and non-drinker trajectory, and those assigned to the intervention or not (with and without exposure to alcohol) over time. Two- and three-way repeated measures analyses of covariance (ANCOVA) will be performed based on region of interest (ROI) scores with covariates such as age, socioeconomic status, pubertal stage, IQ, and other drug use. For cortical thickness and VBM only a-priori defined ROI will be used (i.e., prefrontal lobes, basal ganglia, limbic brain regions and corpus callosum), as previous studies have shown that alcohol affects these regions. For fMRI, we will conduct both exploratory and ROI analyses, and for the DWI data, the regions showing linear age trends in the fMRI analysis will be used as start/finish points for probabilistic tractography.

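### The intervention was allocated by school, but the stated test of the Objective 3 intervention contrast has no school-level error term and its power claim has no design effect

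*Protocol article*

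**What the plan says.** **Allocation.** The section on the Co-Venture Trial states: "This study uses a cluster-randomized controlled design in which 31 schools (cluster) agreed" to take part, and "Schools were randomly assigned to i) be trained and assisted in the delivery of the Preventure programme to Grade 7 high-risk adolescents" or to a no-exposure arm. The school is the unit of randomisation.

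**Objective 3.** Objectives and hypotheses states: "By comparing high-risk youth who received intervention to those who did not, we will estimate an intervention effect on structural and functional brain outcomes". Participants fixes the numbers: "60 high SS (30 of whom will receive the intervention), 60 high IMP (30 of whom will receive the intervention"). That is 60 high-risk youth per arm, 120 in all. The 30 low-risk youth play no part in this contrast.

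**Model.** Statistical analyses lists the comparison by intervention assignment among its aims and gives the method: "Two- and three-way repeated measures analyses of covariance (ANCOVA) will be performed based on region of interest (ROI) scores". The adjustment it names is for characteristics of the participant: "with covariates such as age, socioeconomic status, pubertal stage, IQ, and other drug use". It mentions no school effect, random effect or cluster-robust error.

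**Power.** Sample size justification derives 125 participants for the personality-group effect, with critical F(2, 118) = 3.07 and 85% power, and adds 25 for attrition. For the intervention it offers one sentence, which says that similar power is needed. It gives no separate calculation.

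**The concern.** Arm is constant within school, so the intervention effect is estimated between schools. Adolescents in one school share peers, local drinking culture and the delivery of the programme. If their brain development is even slightly more alike than that of adolescents in different schools, an error term built from differences between individuals understates the variance of the arm comparison.

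Objective 3 is the study's only randomised contrast. The article rests its causal claim on it, and the Discussion expects the results to bear on public policy. Intervals that are too narrow and a false-positive rate above the stated level do most damage here. Objectives 1 and 2 are less exposed, because risk groups and drinking status can vary within a school.

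**Working it through.** **1. The unit counted in the plan's own figure.** An ANCOVA with 3 groups, 4 covariates and 125 participants has denominator degrees of freedom 125 − 3 − 4 = 118, as stated. The 5% critical value of F(2, 118) is 3.073, also as stated. The article gives no numerical effect size for this test. With f = 0.30 (assumed), the noncentrality is 125 × 0.30² = 11.25 and power is 85.1%. So the stated 125 reproduces as a calculation on independent individuals, with no design effect in it. It concerns personality group, but it is the only basis offered for the intervention test.

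**2. Inputs for Objective 3.**
- High-risk youth: 120 (Participants).
- Schools: 31 (Co-Venture Trial section). How many feed the imaging subsample is not in the text shown.
- School ICC: not given. A range of 0.02 to 0.10 is assumed.
- Mean cluster size if all schools contribute: m = 120 / 31 = 3.87.

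**3. Formulas.**
- Design effect: DE = 1 + (m − 1) × ICC.
- The true standard error is √DE times the one reported.
- Actual error of a nominal two-sided 5% test: 2 × [1 − Φ(1.96 / √DE)].
- Effective sample size: 120 / DE.

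**4. Results with all 31 schools (m = 3.87).**

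| ICC (assumed) | DE | SE multiplier | Actual error | Effective N |
|---|---|---|---|---|
| 0.02 | 1.06 | 1.03 | 5.7% | 113 |
| 0.05 | 1.14 | 1.07 | 6.7% | 105 |
| 0.10 | 1.29 | 1.13 | 8.4% | 93 |

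For example, at ICC 0.10: DE = 1 + 2.87 × 0.10 = 1.287, √DE = 1.135, 1.96 / 1.135 = 1.73, and the two-sided tail area is 8.4%.

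**5. Sensitivity to fewer schools.** If only 15 schools contributed (an assumption, m = 8), DE would be 1.14, 1.35 and 1.70 at the same three ICCs, and the actual error 6.6%, 9.2% and 13.3%.

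**6. Degrees of freedom.** A between-school comparison has at most 31 − 2 = 29 degrees of freedom. The 5% critical t is then 2.05, against 1.98 on the 118 that come from counting 120 individuals in two arms (120 − 2). The error rates above use 1.96 and leave this out.

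**7. Illustrative power.** Take d = 0.6, the two-group equivalent of f = 0.30, as a simple two-arm comparison. With 60 per arm, power is 90% if individuals are independent. With 31 schools and 29 degrees of freedom it is 87%, 84% and 80% at ICC 0.02, 0.05 and 0.10. After 15% attrition (51 per arm), 85% falls to 82%, 79% and 75%.

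**The case against.** **Silence is not a decision.** This is a condensed article, the covariate list is open-ended, and an analysis plan not shown may contain a school term. That stands in part: a school term is unstated, not expressly excluded. But the article does name the model, and its power arithmetic counts individuals. Adding a covariate to an open list would not by itself supply the school-level error term that a between-school treatment needs.

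**The relevant ICC is that of change.** The baseline scan precedes the intervention and the contrast is arm by time, so stable differences between schools in brain level cancel. This stands. The ICC in the working must be read as the school ICC of change scores, which could be smaller or larger than that of level. Adjustment for socioeconomic status may also absorb some of the clustering.

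**The size is modest on the documented cluster count.** This stands too. A reader might infer far worse inflation: 10 schools (12 youth each) and ICC 0.10 would give DE = 1 + 11 × 0.10 = 2.10 and an actual error of 17.6%. That needs an assumed small number of schools as well as the top of an assumed ICC range, and the text supports neither.

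**Complete cases.** A reader might also infer that repeated-measures ANCOVA will discard everyone without all three scans. The article does not say so. Attrition is provided for in the numbers ("Another 25 participants will be added to the sample to allow for attrition (15% over 4 years, based on previous studies"), and 150 × 0.85 = 127.5 exceeds the 125 required. This is not a finding.

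**Conclusion.** The point holds for Objective 3. As written, the plan allocates by school, analyses by individual and gives no design effect, so its standard errors are too small for any positive school ICC of change. On the only cluster count documented, and an assumed ICC of 0.02 to 0.10, they are understated by a factor of 1.03 to 1.13. The inflation is larger if fewer than 31 schools contribute; by how much cannot be settled from the text shown. The sentence on power for the intervention is unsupported as it stands, because it carries over an individual-level calculation for a different contrast and a larger sample. The documents do not show that the final analysis will ignore school.

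**What to change.** For the intervention contrast on ROI scores, replace the repeated-measures ANCOVA with a linear mixed model on all available scans, with random effects for participant, school and school-by-time. The school-by-time term is needed because a school intercept alone does not capture clustering of change. School-clustered standard errors with a few-cluster correction are an acceptable alternative. Base the degrees of freedom for the intervention terms on the number of contributing schools, at most about 29, and state that number.

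Replace the sentence on intervention power with a calculation for 120 high-risk youth, stating the assumed effect size, the ICC of change, the number of schools and the attrition.

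The cost is somewhat wider intervals and a less favourable power figure; no new data are needed provided each participant's school is on file, as allocation by school implies. Extending school-level inference to the whole-brain fMRI maps, for example by permuting allocation between schools, would change the group-level procedure in Data analysis. That is more than a change of wording and should be decided separately.

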#### Procedure

Eligible students will be invited to attend three identical scanning sessions over a 5-year period: the first session during the baseline year of the Co-Venture Trial (for intervention schools, this would refer to the period prior to when intervention sessions are run), and second and third session 24 and 48 months later, respectively (Grade 9 and 11). Participants will undergo a 65-min structural and functional neuroimaging assessment, and will complete a 2-h battery of neuropsychological tasks post-scan. In addition, participants will be assessed on substance use, global IQ and behavioral measures annually for 4 years post intervention through the Co-Venture Trial.

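### For objectives 2 and 3, a mixed model on all available scans would serve better than repeated-measures ANCOVA, which in its standard form uses only youths with all three scans

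*Protocol article*

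**What the plan says.** The protocol article, under Statistical analyses, sets the method for comparing risk groups, drinking trajectories and intervention status over time: "Two- and three-way repeated measures analyses of covariance (ANCOVA) will be performed based on region of interest (ROI) scores". The sentence then names five examples of adjustment variables, among them age, pubertal stage and use of other drugs.

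Under Procedure, "Eligible students will be invited to attend three identical scanning sessions over a 5-year period": baseline, 24 months and 48 months. The same section says that "participants will be assessed on substance use, global IQ and behavioral measures annually for 4 years post intervention".

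Under Sample size justification, "An estimated 125 subjects in total will be required to identify a moderate effect of personality group", and then "Another 25 participants will be added to the sample to allow for attrition", put at 15% over 4 years. Over-recruitment is the only response to attrition that the article describes.

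The article describes no mixed model for the ROI scores. The mixed-effects software named under Data analysis is for group-level fMRI maps, and its random-effects variance is forced to zero, so it does not deal with incomplete series of ROI scores.

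**The concern.** Standard repeated-measures ANCOVA takes one row per participant, with the three scans as repeated outcomes and each covariate held at one value. A youth who misses one scan then leaves the analysis, and the scans already acquired are not used.

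Two things are at stake for objectives 2 and 3. The first is information: some precision is lost that the data could supply. The second is selection: if leaving the study is related to drinking or to the brain measures, results in completers need not describe the youths recruited. Objective 3 is a causal contrast between intervention and no intervention, so a selected subset matters there.

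A smaller matter concerns covariates. Pubertal stage and other drug use change between Grades 7 and 11, and one value per person cannot adjust the later scans in the drinker comparison of objective 2.

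**Working it through.** **1. The plan's own figures.** For the baseline test the article gives "with 4 covariates, critical F(2, 118) = 3.07, *p* = 0.05, 85% power". With 3 groups and 4 covariates, the error df are 125 - 3 - 4 = 118, and the 5% critical value of F(2, 118) is 3.073. The effect size f is not stated. With f = 0.30 (assumption) the noncentrality is 125 x 0.09 = 11.25 and power is 0.851, so the figure reproduces. With f = 0.25 power would be 0.695.

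Attrition: 125 / 0.85 = 147.1, so 148 are needed and 150 are planned. Expected completers are 150 x 0.85 = 127.5, above 125.

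**2. Does the stated longitudinal test look like a completer analysis?** The article prints the df as 4240, read here as (4, 240). With 3 groups and 3 visits, classical error df are 2(N - 3) without covariates and 2(N - 3 - 4) with four fixed covariates.
- 2(N - 3) = 240 gives N = 123.
- 2(N - 7) = 240 gives N = 127.
- All 150 youths would give 2 x 147 = 294 or 2 x 143 = 286.

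The stated df therefore fit a classical analysis of about 123 to 127 youths, roughly the expected completers. This is an inference, not a statement in the article.

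**3. Scans left unused at 15% loss.** Leavers: 150 x 0.15 = 22.5. If all leave after scan 1, 22.5 scans are unused; if all leave after scan 2, 45 are. Completers supply 127.5 x 3 = 382.5.

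**4. Information on change.** Assumptions: equal variances, a common correlation r between any two visits, r from 0.3 to 0.8, 15% loss in each group, and no other missing scans. Let s be the share of the variance of the change that the leavers' observed scans do not explain. Efficiency relative to full data is then 1 / (s/0.85 + 1 - s). The complete-case value is 0.85.

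| Change | When leavers go | s | r = 0.3 | r = 0.8 |
|---|---|---|---|---|
| 48 months | after scan 2 | (1 + 2r) / (2(1 + r)) | s = 0.615, 0.902 | s = 0.722, 0.887 |
| 48 months | after scan 1 | (1 + r) / 2 | s = 0.65, 0.897 | s = 0.90, 0.863 |
| 24 months | after scan 1 | (1 + r) / 2 | s = 0.65, 0.897 | s = 0.90, 0.863 |
| 24 months | after scan 2 | 0 (nothing missing) | 1.00 | 1.00 |

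The mixed model thus keeps 0.86 to 0.90 of the information at 48 months and 0.86 to 1.00 at 24 months. The complete-case standard error is larger by a factor of sqrt(0.863/0.85) = 1.01 to sqrt(0.902/0.85) = 1.03 at 48 months, and by at most sqrt(1/0.85) = 1.08 at 24 months.

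**5. Selection bias, as illustration.** In a simulation about 14% missed the 48-month scan, with the chance of missing it depending on the 24-month value in one arm only. Three assumed correlation patterns were used.
- A true 24-month effect of 0.15 SD became 0.09 to 0.11 in completers and stayed at 0.15 using all data.
- A true 48-month effect of 0.30 became 0.27 to 0.30 in completers and stayed at 0.30 with the likelihood estimate.

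The parameters are assumed. The result shows that bias can arise, not how large it will be here.

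**The case against.** The strongest reply is that the article never says incomplete cases are deleted or covariates frozen. It names a method in one sentence, and a long-format fit with participant as a factor could use partial series and changing covariates. A condensed article may leave such details to the full protocol. This stands as far as it goes: a reader might infer that every youth who misses a scan will be dropped, and the text does not say so. But the method itself is fixed, its usual form works on complete series, and the stated df agree with that form.

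Second, the attrition is budgeted. This stands in full. A reader might infer that the study falls short of its planned size, but 127.5 expected completers exceed 125.

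Third, larger losses can be produced by assuming failed scans. With 5% or 10% unusable per session, 0.85 x 0.95^3 = 73% or 0.85 x 0.90^3 = 62% of youths would have all three. The article gives no such rate, so these figures are no evidence of a shortfall.

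Fourth, a reader might infer that every covariate should be updated at each scan. That is wrong for objective 3: drug use after the intervention may lie on its causal path, and adjusting for it could remove part of the effect. Age at each scan is also largely determined by visit, because the cohort is one school grade scanned at fixed intervals. The covariate point therefore has force mainly for pubertal stage and drug use in objective 2.

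**Conclusion.** The point holds in a limited form. For objectives 2 and 3 the named method is, in its standard form, less efficient and more open to selection than a readily available alternative. Objective 1 is unaffected.

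The loss of precision is modest: standard errors about 1% to 3% wider at 48 months and up to about 8% wider at 24 months, if attrition is 15%, correlations are equal and between 0.3 and 0.8, and no other scans are missing. Selection bias is possible but cannot be sized from the article, which does not say how leavers differ from completers. The documents support neither a claim of inadequate sample size nor a claim that deletion is planned. The case for change is that a better method exists at almost no cost.

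**What to change.** Under Statistical analyses, for objectives 2 and 3, replace repeated-measures ANCOVA of ROI scores with a linear mixed model fitted by restricted maximum likelihood to all available scans. Include group, visit, group x visit and a random participant intercept. Keep the complete-case ANCOVA as a sensitivity analysis.

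State the covariate rule by objective:
- **Objective 2:** enter pubertal stage and other drug use at each scan where they are collected. The article documents annual substance-use assessment but does not say when pubertal stage is measured.
- **Objective 3:** adjust for baseline values only.

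The cost is slightly more analysis work. The model relies on data being missing at random given what was observed, a weaker assumption than complete-case analysis needs. It does not remove bias if dropout depends on unobserved outcomes.

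### Structural analyses confined to alcohol-sensitive regions cannot tell a global from a developmentally specific effect if every listed region is affected

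*Protocol article*

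**What the plan says.** **Hypotheses.** In the Protocol article, Objectives and hypotheses, Objective 2 gives competing accounts of what drinking does to the brain. The first reads "Global effects: abnormalities will be observed systematically across all measures of brain function and structure". The second holds that "alcohol-induced abnormalities will be specific to regions and cognitive processes that are maturing in adolescence". Objective 3 puts the same alternative, global or regional, for the effect of the intervention.

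**Structural analysis.** Statistical analyses says: "For cortical thickness and VBM only a-priori defined ROI will be used". The regions follow as a closed list (prefrontal, basal ganglia, limbic, corpus callosum). The reason given is "as previous studies have shown that alcohol affects these regions".

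**Other modalities.** The next sentence is wider: "For fMRI, we will conduct both exploratory and ROI analyses". For diffusion imaging, the tractography end points are regions that show linear age trends in the fMRI analysis.

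**Covariates.** The models are repeated measures ANCOVAs on ROI scores, "with covariates such as age, socioeconomic status, pubertal stage, IQ, and other drug use". Sex is not named there, as factor or covariate. Participants sets a sex quota: "Grade 7 students (50% girls) will be invited to participate in this neuroimaging study". It does not say whether the quota applies within each group.

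**Image processing.** Data analysis computes cortical thickness at 81,924 vertices and segments the T1 image into grey matter, white matter and cerebrospinal fluid. Whole-brain summaries should therefore be obtainable from data already processed.

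**The concern.** To choose between a global and a specific effect, the analysis needs somewhere the two predict different results: a whole-brain quantity, or a region where the specific hypothesis predicts little or nothing. For structure, the plan fixes neither. Every listed region was chosen because an alcohol effect is already expected there, and the word 'only' closes the list.

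The Abstract presents global atrophy versus specific disturbance of maturing processes as an open question that motivates the study. A finding of effects in all four sets of regions could be reported as support for either account, for drinking (Objective 2) and for the intervention (Objective 3).

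The protocol's own theory offers a contrast that the plan does not use. The Background section describes maturation moving from posterior to anterior cortex, with frontal areas late. Posterior cortex would be a natural comparison region, but the restriction shuts it out.

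**Working it through.** **1. What each hypothesis predicts.** Let g be an effect common to the whole brain and s an additional effect in a region, on the same scale. The effect seen in a region is g + s. Let w be the share of the whole-brain mean contributed by the affected regions, between 0 and 1. The documents do not give w, so it stays a symbol.

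| Situation | Effect in listed regions | Effect on whole-brain mean | Region minus mean |
|---|---|---|---|
| A. Global only (s = 0) | g in all | g | 0 |
| B. Specific, all listed regions affected (g = 0) | s in all | w × s | s − w × s = (1 − w) × s |
| C. Specific, some listed regions affected (g = 0) | s in some, 0 in others | w × s | differs between regions |

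The structural plan as written observes only the second column.

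- A and B look the same there: an effect in every listed region.
- C differs from A, so a patchy result counts against the global hypothesis even under the present plan.
- The whole-brain mean alone does not settle A against B, because it is non-zero in both. The last column does: zero under A, non-zero under B.
- Because the mean contains the listed regions, the last column shows (1 − w) × s rather than s. The regional effect is somewhat understated, so the adjusted result is conservative. Adjustment by a covariate works in a similar way but not identically.

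**2. Cost, starting from the plan's own figure.** Inputs from Sample size justification: 3 groups, N = 125, 4 covariates, critical F(2, 118) = 3.07, α = 0.05, power 85%. The effect is called moderate, with no value given.

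Formula: noncentral F with noncentrality N × f², numerator df 2, denominator df N − 3 − q for q covariates.

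- With q = 4: df = 125 − 3 − 4 = 118 and critical F = 3.073, as stated. At f = 0.30 the noncentrality is 125 × 0.09 = 11.25 and power is 85.2%. The smallest N for 85% is 125, so the figure reproduces.
- This relies on f = 0.30. At f = 0.25 power would be 69.5% and the required N 178.
- With q = 7 (the five named covariates, sex and one whole-brain measure): df = 125 − 3 − 7 = 115 and critical F = 3.075. Power at f = 0.30 is 85.1%, and the required N is still 125.
- Unrounded, power moves from 85.15% to 85.12%, a loss of 0.03 percentage points. Any variance the added covariates explain would raise it.

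This calculation is for the baseline comparison of three groups. It serves here as a guide to what extra covariates cost.

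**3. Sex.** If sex is left out, the bias in a group contrast is the sex difference in SD times the difference in the share of girls. For an assumed sex difference of 0.2 to 0.8 SD:

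- equal shares: 0;
- shares 10 points apart: 0.2 × 0.10 = 0.02 to 0.8 × 0.10 = 0.08 SD;
- shares 20 points apart: 0.2 × 0.20 = 0.04 to 0.8 × 0.20 = 0.16 SD.

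If the quota holds within the recruited risk groups, the first line applies to them at enrolment. Drinkers and non-drinkers are defined after enrolment, so the quota does not balance that comparison.

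**The case against.** **The covariate list is illustrative.** It is introduced as examples, in a condensed article, and full lists are commonly left to the analysis plan. A reader might infer that the models omit sex and head size, but the text does not show that. This stands, and it makes sex a secondary matter. It does not rescue the structural restriction, which is a stated choice of what will be analysed.

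**Head size is a weaker worry than it looks.** T1 images are registered to stereotaxic space before segmentation, which may remove some head-size variation for VBM. Stable head size also largely cancels in within-person change. This stands. What remains concerns mainly the baseline VBM comparison in Objective 1.

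**The hypotheses do not predict the same thing in general.** A reader might infer that the study cannot separate them at all. That goes too far. A patchy regional pattern speaks against a global effect, differences between listed regions are informative about relative effects, fMRI has an exploratory arm, and the cognitive tests span several domains. All of this stands and limits the point to situation A against B in the structural data.

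**Adjusting for a global measure is one convention among several.** Mean thickness includes the regions under test, and a truly global effect would act through it. This is also correct, which is why the adjusted result should be shown beside the unadjusted one and read as relative specificity.

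**Conclusion.** The point holds for cortical thickness and VBM. The plan limits these to regions already expected to respond to alcohol and names no whole-brain measure or comparison region. If all of them show an effect, the structural data cannot distinguish the global from the developmentally specific hypothesis in Objectives 2 and 3. If only some do, or if other modalities are brought in, partial information remains.

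The size is best stated as which result becomes uninterpretable: a uniform effect across the listed regions. The documents give no basis for putting a probability on that result. The conclusion rests on reading the closed list and the word 'only' as binding.

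Naming sex is a secondary improvement. Its bias figures depend on an assumed sex difference and an assumed imbalance, and the documents show neither.

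**What to change.** Amend the sentence that limits cortical thickness and VBM to a-priori regions, as follows.

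1. Test a whole-brain structural measure from the same T1 pipeline directly for the global hypothesis, for example mean cortical thickness or total grey matter volume.
2. Report each structural regional effect without and then with adjustment for that measure, taken at the same visit so that change over time is adjusted too. Alternatively, contrast the listed regions with comparison regions not expected to be maturing, such as posterior cortex. Read the adjusted effect as relative regional specificity, and note that it is somewhat conservative because the whole-brain measure contains the listed regions.
3. Name sex as a covariate, and state how head size is handled for VBM.

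The cost is one or two degrees of freedom, with power and N essentially unchanged. No new data are needed: sex should already be known, since recruitment uses a quota on it, and the whole-brain measures should come from images that will be processed anyway.
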